### Comparison condition

Participants in the comparison site will receive usual care at the B&GC (standard programming) during the study and complete assessments at baseline, 2 and 6 months follow up. The comparison B&GC site will receive an intervention toolkit including intervention materials, protocols, and supplies upon study completion.

### Intervention fidelity

Several strategies will be utilized to maximize intervention fidelity. Prior to study start, the research team will provide in-depth training sessions on all intervention materials and study procedures for B&GC health program staff. The training consists of a comprehensive intervention protocol review, didactic and discussion-based sessions, and mock sessions with feedback provided by research staff. Intervention delivery will be supervised by the PI and 1–2 trained research assistants. Research team members will attend and complete intervention fidelity checks during each intervention session to assess the extent to which intervention activities were completed as designed. Intervention fidelity checks consist of a list of protocol activities for which the extent of fidelity was rated on a scale of 0 to 2 (0 = did not do this activity; 1 = partially completed; 2 = completed), space for comments regarding each activity, and duration of intervention session.

### Participant recruitment

Screening and recruitment will be conducted by the study team (PI, research coordinator) and B&GC staff. The PI will train the research coordinator and B&GC staff in implementing the screening and recruitment protocols and oversee the screening and recruitment process through weekly in-person meetings. In collaboration with B&GC staff at each study site, the PI will design a fact sheet to introduce the study to potential child and parent/caregiver participants. Recruitment packets containing the fact sheet, study eligibility, consent forms, and study procedures will be provided to B&GC staff to distribute among youth within the eligible age range (9–12 years) and parents/caregivers of youth within this age group. B&GC staff will also verbally inform youth of the study, presenting it as a healthy habits program in order to avoid explicit announcement of the underlying hypotheses about SSB consumption and obesity risk.

After an initial pool of interested youth are identified, the research coordinator and B&GC staff will screen youth for eligibility (details provided in Study Setting and Population). The research coordinator will provide further explanation of the study, review study assent forms, and answer questions. The PI will also be available to answer questions and address concerns. Interested and eligible youth will be given study recruitment packets containing study information and consent forms for parents/caregivers. During pick-up time at the B&GC, the research coordinator will meet with parents/caregivers of interested and eligible youth participants, screen parents/caregivers for eligibility (details provided in Study Setting and Population), provide further explanation of the study, review study consent forms, and answer questions. All participants will be informed procedures to protect the confidentiality of data collected and that their care at the B&GC would be in no way affected by study participation. Interested and eligible parent–child pairs will be asked to complete three written consent forms (child assent to participate, parental consent for their child to participate, and parental consent to participate as a study participant). Only parent–child pairs who complete all three forms will be enrolled in the study. Enrolled child and parent/caregiver participants will be asked to complete baseline assessments prior to the intervention start date.

### Study measures

Study assessments will be led by trained researchers and conducted at B&GC sites at baseline and two follow-up time points (2 and 6 months post-baseline).

### Feasibility outcomes

The number of parent–child dyads available for recruitment and retention using a CONSORT diagram [28, 29] and the number and reasons for failure to complete follow-up assessments will be reported. To assess intervention engagement, B&GC staff in the intervention site will track child intervention session attendance rates, number of narrative materials completed per child, percent of parent–child take-home activities completed, and parent and child attendance rates of the family viewing celebration.

Immediately following intervention completion, parent and child participants will rate/report the following indicators on intervention satisfaction and acceptability: overall satisfaction with each intervention component (youth sessions, narrative materials, parent–child take-home activities, and Club open house event); likelihood of referring intervention to a friend; likelihood of participating in a similar intervention targeting a different dietary behavior; intervention aspects perceived to be most useful; and suggestions to improve the intervention. A 5-point Likert scale will be used to assess outcomes 1–4; open ended responses will be used to assess outcomes 5–6.

### Efficacy outcomes

The primary outcomes, child and parent consumption of SSBs and water (frequency, type, and servings of SSBs and water consumed on a typical day in the past 7 days) will be assessed using items from the Youth Risk Behavior Surveillance Survey [30] and a validated youth food-frequency questionnaire (FFQ) [31]. Secondary outcomes (knowledge related to SBBs and water, self-efficacy to reduce SSB intake and drink water) will be assessed among children and parents using modified items from validated surveys [32, 33]. Child height, weight, and waist circumference will be measured at each assessment point using portable digital scales, stadiometers, and tape measures with the participant wearing light clothing and no shoes; measurements will be taken to 2/10^th^ of the nearest inch or pound. Body mass index will be calculated as weight (kg)/height (m^2^). Youth Risk Behavior Surveillance Survey items [30] will be used to assess children’s other dietary behaviors, such as frequency of fruit, vegetable, breakfast, and fast food consumption and intake of non-SSBs (i.e., diet drinks, water, 100 % fruit juice), and children’s physical activity and sedentary behaviors (i.e., frequency and duration of moderate-to-vigorous physical activity and screen time activities). Covariates of interest will be assessed through self-report surveys and include child and parent gender, race/ethnicity, and age; child eligibility for free/reduced priced lunch; and parental education, income, and employment status.

### Power calculation

Our sample size calculations are based on the primary hypothesis that child participants in the intervention site will have reduced SSB intake and increased water intake than child participants in the comparison site at 2 and 6 months follow-up. Results from our pilot data indicate that B&GC children consumed an average of 7.6 servings of SSBs over the past 7 days (SD = 6.5). Assuming that youth in the comparison site will experience no change in SSB intake from baseline to follow-up, a two-sided, two-sample t-test of means with alpha = 0.05 and 80 % power indicates that enrolling 45 children per group will allow us to detect a difference of 3.9 servings of SSBs per week, a clinically meaningful difference of approximately 550–940 kcals per week depending on serving size and SSB type. To account for 20 % dropout, we will enroll 54 parent–child pairs (*N* = 108) per site, yielding a total sample size of 216 participants.

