### Analysis plan for feasibility and efficacy outcomes

For feasibility outcomes, recruitment and retention rates will be compared across study sites and t-tests will be used to compare overall rates between the two sites. The number and reasons for failure to complete follow-up assessments will be reported. To analyze intervention engagement, youth session attendance rates for each session, percent of parent–child activities completed per week, number of narrative materials produced per child, and parent and child attendance rates at the club open house event will be reported. Intervention fidelity rates per session will be reported, and reasons for poor fidelity will be explored. For intervention acceptability and satisfaction, we will report descriptive statistics of intervention satisfaction ratings among children and parents and the proportions of children and parents who would recommend the intervention to others.

Distributions, descriptive statistics, and missing values will be examined for all efficacy study variables. Bivariate analyses will compare the characteristics of the intervention and comparison groups using two-tailed chi-square tests for categorical variables and two-tailed t-tests for continuous variables. These results will identify imbalances between groups that will be adjusted for in multivariable analyses. All analyses will utilize an intent-to-treat approach, with each child and parent participant enrolled in the intervention site analyzed as part of the group, regardless of intervention engagement. We will compare mean changes in our primary outcome (children’s SSB intake frequency) and secondary outcomes across intervention conditions using repeated measures mixed models. Generalized estimating equations will be used to account for clustering of observations within sites. Based on the relatively small sample size, complete case analysis with comparisons with baseline data will be used to address missing data as a result of loss to follow up.

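### The trial is sized on weekly SSB servings at one visit but analysed as change in SSB intake frequency, so the stated 80 % power is not shown for the endpoint analysed.

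*Protocol article*

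**What the plan says.** Three sections of the protocol article describe the child SSB outcome, each differently.

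- **Power calculation.** The variable is servings over a week. The pilot input is that "children consumed an average of 7.6 servings of SSBs over the past 7 days (SD = 6.5"; the test is "a two-sided, two-sample t-test of means with alpha = 0.05 and 80 % power"; the result is that "enrolling 45 children per group will allow us to detect a difference of 3.9 servings of SSBs per week". The section attaches a clinical meaning of about 550–940 kcal per week to that difference. It also sets out an assumption about the comparison site: "Assuming that youth in the comparison site will experience no change in SSB intake from baseline to follow-up".
- **Analysis plan for feasibility and efficacy outcomes.** "We will compare mean changes in our primary outcome (children’s SSB intake frequency) and secondary outcomes across intervention conditions using repeated measures mixed models". Here the variable is frequency and the contrast is change.
- **Efficacy outcomes.** The primary outcomes cover frequency, type and "servings of SSBs and water consumed on a typical day in the past 7 days". Frequency and servings are listed as separate items, the recall unit is a typical day, and no single variable is selected.

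The article gives no SD of change, no correlation between baseline and follow-up, no mean, SD or target difference for frequency, and no intraclass correlation. Study aim and design states that there are two sites, one per arm. The Abstract repeats the 80 % power and the 3.9 servings.

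**The concern.** A power statement belongs to one variable and one contrast. Here it belongs to servings per week compared with a single-visit SD, while the analysis names change in frequency.

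Two things follow. First, with no inputs for frequency, power for the analysis as worded cannot be computed, and a change in frequency cannot be turned into servings or kilocalories without portion data. The trial could then report a result that cannot be set against the difference it calls clinically meaningful. Because both frequency and servings are collected, leaving the choice open also allows the variable to be picked after the data are seen.

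Second, even if frequency is loose wording for servings, a change score has a different SD from a single visit. The two are equal at only one value of the baseline-to-follow-up correlation, and the article does not give that correlation.

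**Working it through.** **Inputs from the Power calculation section:** SD 6.5 servings per week, difference 3.9, two-sided alpha 0.05, 45 analysed per group. **Assumptions (not in the article):** the correlation r between any two visits, equal variances at all visits, and, where used, the intraclass correlation (ICC).

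**1. The plan's own figure.** Standardised difference = 3.9 / 6.5 = 0.60. The two-sample t-test needs 44.6, so 45 per group; power at 45 is 80.4 %. The stated figure reproduces, for servings with a single-visit SD.

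**2. Analysis of change in frequency, as worded.** No mean, SD or target is given, so no power can be calculated.

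**3. If the analysis is change in servings.**

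- Change to one follow-up: SD = 6.5 × √(2(1 − r)). At r = 0.3 this is 6.5 × √1.4 = 7.69; at r = 0.5 it is 6.5 × √1 = 6.50.
- Change from baseline to the average of the 2- and 6-month values: the variance factor is (1 + r)/2 + 1 − 2r = 1.5(1 − r), so SD = 6.5 × √(1.5(1 − r)). At r = 0.3 this is 6.5 × √1.05 = 6.66.
- One follow-up adjusted for baseline: SD = 6.5 × √(1 − r²). At r = 0.3 this is 6.5 × √0.91 = 6.20.

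Power at 45 per group for a true difference of 3.9 (t-test), with no between-site variance:

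| Assumed r | Change, one follow-up | Change, both follow-ups averaged | Baseline-adjusted, one follow-up |
|---|---|---|---|
| 0.3 | 66 % | 78 % | 84 % |
| 0.4 | 73 % | 84 % | 87 % |
| 0.5 | 80 % | 90 % | 90 % |
| 0.7 | 95 % | 99 % | 98 % |

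Change to one follow-up keeps 80 % only when r is about 0.5 or more. At r = 0.3 it would need about 62 per group, and its detectable difference at 45 is 4.6 servings, against 3.7 with baseline adjustment.

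**4. Why baseline adjustment gives a floor.** √(1 − r²) is never above 1, so the adjusted SD is never above 6.5 and power at 45 analysed is never below 80.4 %, whatever r is. The floor is tied to 45 analysed: 54 enrolled less 20 % leaves 54 × 0.8 = 43.2, and at 43 it is 78.5 %.

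**5. What the floor leaves out.** With one club per arm, site variance multiplies the variance of the difference by 1 + (n − 1) × ICC. At n = 45 and ICC 0.02 this is 1 + 44 × 0.02 = 1.88. For the baseline-adjusted analysis at r = 0.5 (normal approximation), power is 91 % at ICC 0, 78 % at 0.01, 67 % at 0.02 and 45 % at 0.05. These figures treat the site variance as known, which two clubs cannot supply. An analysis that ignores it has a type I error of about 10 %, 15 % and 27 % at those three non-zero ICCs.

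**The case against.** - **Frequency may be loose wording for servings.** This is possible, since the Efficacy outcomes section lists both and a daily figure can be multiplied up to a week. But that section treats them as different quantities and the article never states the conversion. The request to reconcile the sections stands either way.
- **The single-visit SD is not an error in itself.** The stated hypothesis concerns a difference between sites at follow-up, and a cross-sectional SD suits that. This is right, and it is why the calculation works as a floor once baseline is a covariate. It does not carry over to a comparison of mean changes.
- **A shortfall is not shown.** A reader might infer from the 66 % that the trial is underpowered. The document does not support that: r is not given, at 0.5 or above the sizing is adequate or conservative, and the planned repeated-measures model may use both follow-ups, which lifts 66 % to 78 % at r = 0.3. Model contrasts may also be settled in a full analysis plan that is not shown.
- **Baseline adjustment is not clearly better with two clubs.** Its usual advantage assumes groups equal in expectation at baseline. Two particular clubs may differ, and with a noisy self-report the adjusted estimate can then keep some bias, while the change score is the less biased one if the clubs would otherwise move in parallel. This stands, and is why both estimates should be shown. The plan to adjust for baseline imbalances does not expressly include baseline SSB intake.
- **A reader might also infer that baseline adjustment secures the power.** It does not. It reduces between-child variance only; site and treatment remain confounded, and neither a mixed model nor generalized estimating equations can estimate between-site variance from two clusters.

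**Conclusion.** The point holds as an inconsistency between the power calculation and the analysis. The 80 % power and the 3.9-serving target are stated for weekly servings at one visit, and the analysis is stated for change in frequency. Power for frequency cannot be derived from the article.

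Read as change in servings to one follow-up, power at 45 per group runs from 66 % (r = 0.3) to 95 % (r = 0.7), reaching 80 % at about r = 0.5; with both follow-ups averaged it is 78 % at r = 0.3 and 84 % at r = 0.4. These figures assume equal variances at all visits, equal correlations between them, and no between-site variance. The article supports no particular r, so the conclusion is that the power is undemonstrated, not that it is low.

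This should be corrected: the remedy is nearly free and makes the result readable against the plan's own target. The reliance on one club per arm is a larger limitation, and this correction does not remove it.

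**What to change.** 1. In Efficacy outcomes, Power calculation and the analysis plan, name one primary child variable: total SSB servings per week. State the SSB types summed, the recall period, and the conversion (typical-day servings × 7, if that is the recall used).
2. In the repeated-measures model, analyse follow-up servings with baseline servings as a covariate, and state whether the contrast is at one follow-up or across both.
3. Report the change-score estimate alongside, because the two clubs may differ at baseline and the two estimates can then disagree.
4. Restate the power for that analysis: at least 80 % with 45 analysed per site for any r, for between-child variance only, and conditional on no between-site variance. Say that one site per arm confounds site with treatment. Unless sites are added to each arm, present the efficacy result as preliminary and specific to these two clubs.

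Items 1 to 4 are changes of wording, and baseline and follow-up servings are already to be collected. The cost is that two estimates may differ and need explaining. Adding sites would be a real cost and a separate decision.

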**Methods:**

Guided by the Social Cognitive Theory and the Social Ecological Model, the H_2_GO! intervention consists of 6 weekly sessions that target beverage knowledge, attitudes, and behaviors through youth-produced messages and narratives to reduce SSB intake and encourage water intake and parent–child activities. To reach underserved youth and families, we identified Boys & Girls Clubs (B&GC) (youth-based community centers that serve an ethnically diverse and predominantly low socioeconomic status population) as a community partner and study setting. Participants (children ages 9–12 years and their parents) will be recruited from B&GC sites in Massachusetts, USA. Intervention efficacy will be assessed through a site-randomized trial (*N* = 2 youth-based community sites, pair-matched for size and racial/ethnic composition) with 54 parent–child pairs (*N* = 108) enrolled per site (*N* = 216 total). The comparison site will carry on with usual practice. Child and parental SSB and water consumption (primary outcomes) and parent and child beverage knowledge and attitudes (secondary outcomes) will be measured via self-report surveys. Additional outcomes include children’s anthropometric data, additional dietary behaviors, and physical activity. Measures will be collected at baseline, 2 and 6 months follow-up. With an estimated 20 % dropout rate, the study will have 80 % power to detect a group difference of 3.9 servings of SSBs per week.

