## Methods

### Study aim and design

This study aims to assess the feasibility and efficacy of a community-based behavioral intervention (delivered through B&GC sites) targeting SSB and water consumption among 108 parent–child pairs (*N* = 216) through a site-randomized trial. The site-level intervention will take place at two B&GC sites that were pair-matched for size and racial/ethnic composition. One site will be randomized to receive the intervention and the other site will receive usual care. The 6-week intervention consists of weekly group-based sessions with assessments conducted at baseline, 2 and 6 months follow-up (see Fig. 1 for study design). The primary outcomes are child and parental SSB and water intake, assessed via validated survey items. Secondary outcomes include child and parental knowledge and attitudes related to SSBs. Additional outcomes include children’s anthropometrics (height, weight and waist circumference), other dietary behaviors, and physical activity. We hypothesize that child participants in the intervention site will demonstrate reduced SSB intake and increased water intake compared to participants in the comparison site at 2 and 6 months follow-up. Study protocol and procedures were approved by the Boston University Medical Center Institutional Review Board.

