## Discussion

Community-based and narrative-based intervention strategies hold potential for decreasing SSB consumption and associated obesity risk among youth and families, particularly among socioeconomically disadvantaged and racial/ethnic minority populations who face disproportionately high obesity rates. Findings from this study will be used to assess efficacy on reducing SSB consumption among youth and families in the USA. If efficacious, the intervention has high potential for dissemination across youth-based settings and will serve as a community-based intervention model to target SSB and water consumption and disparities in childhood obesity.

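### The stated 80% power and two-sided 5% error hold only if there is no between-site variance, which a trial with one site per arm cannot estimate

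*Protocol article*

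**What the plan says.** **Allocation.** Study aim and design describes two clubs, matched for size and racial/ethnic composition: "One site will be randomized to receive the intervention and the other site will receive usual care".

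**Sample size.** The Power calculation section uses "a two-sided, two-sample t-test of means with alpha = 0.05" and a pilot SD of 6.5 servings over 7 days. It reports that "80 % power indicates that enrolling 45 children per group" "will allow us to detect a difference of 3.9 servings of SSBs per week". It contains no ICC, design effect or other site term. The abstract carries the result over as an unconditional property: "the study will have 80 % power to detect a group difference of 3.9 servings of SSBs per week".

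**Analysis.** The analysis plan section compares mean changes with repeated measures mixed models, adjusts for baseline imbalances, and assigns the clustering of children within sites to GEE.

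**Purpose.** Study aim and design names feasibility and efficacy together. The Discussion says: "Findings from this study will be used to assess efficacy on reducing SSB consumption among youth and families in the USA".

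**The concern.** A two-sample t-test of children takes each child as an independent unit. Here children share a site, and the site is what is allocated. Anything that changes SSB intake in one club's children and not the other's over the 2 to 6 months of follow-up enters the treatment contrast in full. Enrolling more children in the same two clubs does not average it out.

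A difference judged significant at the stated 5% level could therefore be a site difference. The reader would have been told that the false-positive risk is 5% and the power 80%, when neither follows from the design. The Discussion links an efficacious result to wider dissemination, so the inference has consequences.

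**Working it through.** **Step 1: reproduce the plan's figure.** Inputs from Power calculation: difference 3.9, SD 6.5, two-sided alpha 0.05, power 80%, 45 per group.
- Standardised difference: 3.9/6.5 = 0.6.
- Exact t-test: n = 44.6, so 45 per group; power at 45 is 0.804; detectable difference at 45 is 3.88.
- Normal approximation: SE = 6.5 × √(2/45) = 1.37; 3.9/1.37 − 1.96 = 0.89; power 0.812.

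The plan's arithmetic is right, but only with children independent and no site term.

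**Step 2: what follows from the allocation alone, with no assumption about the ICC.**
- Degrees of freedom for between-site variance: 2 sites − 2 arms = 0.
- Two sites have two possible allocations, so the smallest randomisation p-value is 0.5 one-sided and 1.0 two-sided. No test based on the allocation can reach 0.05.
- The robust variance in GEE relies on variation between independent clusters in the same arm. With one cluster per arm there is none. A mixed model cannot separate a site effect from the arm effect either.

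**Step 3: illustration of size.** The document gives no ICC, so 0.01, 0.02 and 0.05 are assumptions. SD is 6.5 (levels, not change), with m = 45 per site.
- Design effect: DE = 1 + (45 − 1) × ICC
- SE = 6.5 × √(2 × DE/45)
- Type I error of the child-level t-test: 2 × [1 − Φ(1.987/√DE)]
- Power at a true 5% level, ICC known: Φ(3.9/SE − 1.96)
- Detectable difference at 80% power, ICC known: 2.80 × SE
- SD of the chance difference between two sites: 6.5 × √(2 × ICC)

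| Assumed ICC | DE | SE | Type I error | Power for 3.9 | Detectable difference | SD of site difference |
|---|---|---|---|---|---|---|
| 0.01 | 1.44 | 1.64 | 10% | 66% | 4.6 | 0.9 |
| 0.02 | 1.88 | 1.88 | 15% | 55% | 5.3 | 1.3 |
| 0.05 | 3.20 | 2.45 | 27% | 36% | 6.9 | 2.1 |

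A simulation (200,000 runs per ICC) in which the t-test uses the within-site SD gave type I errors of 10, 16 and 28%.

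**Step 4: would more children help?** With unlimited children per site the SE falls only to 6.5 × √(2 × ICC). At ICC 0.05 that is 2.06, and power is Φ(3.9/2.06 − 1.96), about 47%. No enrolment figure at two sites restores both stated properties.

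**The case against.** **Clustering is already handled, and the t-test only sizes the study.** It is true that the t-test is not the planned analysis. The type I errors above therefore belong to a child-level t-test on levels. A reader might take them as the error rate of the planned models, but the document gives neither the SD nor the ICC of change, so it does not support that. What does not stand is the claim that GEE resolves the clustering, for the reason in step 2.

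**Changes from baseline are compared, with adjustment for imbalances.** This stands in part. A reader might infer that any site difference in intake will be read as an intervention effect. That goes too far: a stable difference in level, such as constant local retail, largely cancels in a comparison of changes. Site-specific change over time remains confounded with arm. The sizing premise "Assuming that youth in the comparison site will experience no change in SSB intake from baseline to follow-up" supposes such change away for the comparison site; it does not protect against it.

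**The sites were matched.** A reader might point to total enrolment in Table 1, 1619 against 1087 (49% higher), as proof that they are unlike. That is selective: daily attendance is 180 against 211 (17% higher), and the listed ethnic groups differ by 1 to 4 percentage points. Nor does enrolment show between-site variance in SSB intake. Matching may well have reduced that variance, but two sites cannot show by how much.

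**Feasibility is an equal aim.** It is, with its own outcomes and analysis, and nothing here touches it. The efficacy aim is nevertheless explicit and is the one the power figure serves.

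**Conclusion.** The point holds as a stated property that the design does not supply. The 80% power and the two-sided 5% error are correct for independently allocated children. For two allocated sites they require site-specific differences in SSB change to be exactly zero, a condition the document does not state and two sites cannot check. This conclusion needs no ICC.

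The size is uncertain. Under assumed ICCs of 0.01 to 0.05 on intake levels, type I error for a child-level t-test would be about 10 to 27%. If the ICC were known, power for 3.9 servings would be about 66 to 36%, and the detectable difference about 4.6 to 6.9 servings per week. Figures for change scores could be smaller or larger. The documents do not support saying that the power or error rate of the planned analysis takes any particular value.

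Because the headline power figure and the efficacy inference both rest on this condition, the text should be corrected.

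**What to change.** 1. **Abstract and Power calculation:** state that 80% power and 5% error assume no between-site variance, that two sites cannot estimate that variance, and that the detectable difference is larger if it is not zero. Give the range as a sensitivity analysis labelled with its assumed ICCs and with the condition that the ICC is treated as known.
2. **Analysis plan:** remove the claim that GEE accounts for clustering by site. Say instead that site and arm cannot be separated.
3. **Abstract, Study aim and design, and Discussion:** keep the efficacy aim but qualify it as preliminary effect estimation. Report the effect as an estimate with an interval and an ICC sensitivity analysis, not as a confirmatory test.

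The cost is a less favourable stated figure and a more modest conclusion. No extra sites, children or measurements are needed. Restoring both stated properties, rather than qualifying them, would require more sites per arm.

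### 54 pairs per site do not cover 20% dropout: about 43 children per site remain, not the 45 that the power statement needs

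*Protocol article*

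**What the plan says.** The Power calculation section names the method as "a two-sided, two-sample t-test of means with alpha = 0.05 and 80 % power". It takes the standard deviation of 6.5 servings per week from pilot data and concludes that "enrolling 45 children per group will allow us to detect a difference of 3.9 servings of SSBs per week". The next step sets the enrolment: "To account for 20 % dropout, we will enroll 54 parent–child pairs" at each site, which makes 108 pairs and 216 participants in total.

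The Methods paragraph of the abstract repeats the enrolment and ties the power to the dropout: "With an estimated 20 % dropout rate, the study will have 80 % power to detect a group difference of 3.9 servings" per week.

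The section on the analysis plan for feasibility and efficacy outcomes says that loss to follow-up will be handled by complete case analysis.

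**The concern.** A dropout rate is a fraction of those enrolled, so the number needed at the end must be divided by one minus the rate. The printed 54 is exactly 45 multiplied by 1.2. That adds 20% of the completers rather than allowing for the loss of 20% of the enrolled.

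If that is how 54 arose, the power quoted for 45 children per group does not apply after the dropout that the protocol itself expects. The abstract attaches the 80% power and the 3.9 servings to the situation after dropout, so the error would sit in the trial's headline design figure. There is no slack to absorb it, because 45 is the smallest whole number per group that reaches 80% power.

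**Working it through.** **Inputs, all from the protocol article**

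- Two-sided two-sample t-test, alpha 0.05, power 80% (Power calculation)
- SD 6.5 servings per week (Power calculation, pilot data)
- Difference 3.9 servings per week, so the standardised difference is 3.9 / 6.5 = 0.60
- 45 children needed per group, 20% dropout, 54 pairs enrolled per site (Power calculation; enrolment and dropout also in the abstract)

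**Step 1: reproduce the base figure.** Power comes from the noncentral t distribution with 2n − 2 degrees of freedom and noncentrality 0.60 × √(n/2). Solving for 80% power gives n = 44.6, so 45 per group. Power is 80.4% at n = 45 and 79.5% at n = 44. The protocol's 45 is correct for its inputs.

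**Step 2: the dropout allowance.**

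- Required enrolment: 45 / (1 − 0.20) = 56.25, so 57 per site (114 pairs, 228 participants)
- Stated enrolment: 54 per site (108 pairs, 216 participants), which equals 45 × 1.20
- Shortfall: 57 − 54 = 3 pairs per site
- Completers from 54 at 20% loss: 54 × 0.80 = 43.2, so about 43
- Largest loss that still leaves 45: (54 − 45) / 54 = 16.7%

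Other starting points do not give 54 either. The unrounded t-test figure gives 44.6 / 0.8 = 55.7, so 56. The normal-approximation figure of 44 gives 44 / 0.8 = 55.

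**Step 3: what the remaining numbers deliver** (t-test, SD 6.5)

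| Children analysed per site | Power for 3.9 servings/week | Difference detectable with 80% power |
|---|---|---|
| 45 | 80.4% | 3.88 |
| 44 | 79.5% | 3.93 |
| 43.2 | 78.7% | 3.96 |
| 43 | 78.5% | 3.97 |

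At 43 per site, power is 1.5 points below the 80% target, and the detectable difference is 3.97 − 3.88 = 0.09 servings per week larger than at 45. To one decimal it is 4.0 rather than 3.9.

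**The case against.** The strongest reply is that the discrepancy barely exceeds the precision of the printed figures. The SD is a pilot estimate given to one decimal. If its unrounded value were 6.45, the lowest that rounds to 6.5, the detectable difference at 43 per site would be 3.97 × 6.45 / 6.5 = 3.94, which still prints as 3.9. The normal approximation with SD 6.5 gives 3.93, with power of 79.4%. This shows that the effect is small. It does not make the statement right, because the protocol names the t-test, prints 6.5 and asks for 45.

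Two points are inferred rather than stated. The protocol prints no inflation formula, so the multiplication by 1.2 is deduced from the exact match. It also does not say whether the 20% applies by 2 months or by 6 months, so more than 43 children may be available at the earlier visit. Neither point rescues the figure: 54 × 0.8 is below 45 however 54 was reached, and the abstract attaches its power claim to a 20% loss without qualification.

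A further objection is that 78.5% does not describe this trial's real power either. The calculation treats children as independent although one site is randomised to each condition, and it uses the SD of a single measurement although changes will be compared. That is a fair limit on any restated figure. It is a separate and potentially larger question, and it does not make the dropout arithmetic correct.

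**Conclusion.** The point holds. On the protocol's own test, SD and dropout rate, 54 pairs per site leave about 43 children per site. That gives 78.5% power for 3.9 servings per week, or 80% power for about 4.0. The abstract's claim of 80% power for 3.9 servings at 20% dropout is therefore not delivered.

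This is a small arithmetic error: three pairs short at enrolment and about two analysed children short per site. It does not threaten the trial. It deserves correction because it affects a stated design figure and is easily put right.

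The conclusion assumes that dropout means 20% of enrolled children, that those lost do not contribute to the comparison (as complete case analysis implies), and that children are independent (as the protocol's t-test supposes).

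**What to change.** Keep 54 pairs per site and correct the statement in both the abstract and the Power calculation section, in one of two ways:

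1. Keep the expected dropout at 20% and restate the result: about 43 children per site are expected to complete, giving 80% power to detect 4.0 servings per week (78.5% for 3.9). The energy equivalent in the Power calculation section should then move too. In proportion, 550 × 4.0 / 3.9 = 564 and 940 × 4.0 / 3.9 = 964, so about 560–960 kcal per week.
2. Keep 80% power for 3.9 servings per week and state that the enrolment allows for 16.7% dropout.

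The first is preferable if 20% is still the expected loss. Either way, add a clause saying that the figure comes from a t-test on individual children and makes no allowance for clustering by site, so that it is not read as the trial's full power.

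The cost is a change of wording in two places, with no extra enrolment. Holding 3.9 servings at 20% dropout would instead take 57 pairs per site, six more pairs in all.
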